#### Secondary Aim - Behavioral and Psychological Processes

The behavioral component of Aim 2 tests the same three alternative hypotheses about which prescription is superior to the others in terms of: a) increasing substitution of healthful for unhealthful eating and activity behaviors, b) promoting elasticity for unhealthful behaviors, and c) promoting inelasticity for healthy behaviors. Substitutability analyses will be performed on cross-consumption coefficients from PDA eating and activity data and behavioral economic laboratory data. Cross-price elasticities from the Want Task will additionally test whether those results match the ones derived from consumption data. Analysis of own price elasticities from the Want task will test the same three hypotheses regarding which prescription best promotes the desired healthier outcome: increased elasticity for sedentary behavior and saturated fat intake, and increased inelasticity for physical activity and fruit and vegetable intake. The form of these analyses will parallel those procedures specified for the primary aim.

The psychological component of Aim 2 tests which behavioral prescription has the most desirable effects on increasing attentional bias, craving, self-efficacy, and positive mood associated with healthy foods and activities, and decreasing those processes for unhealthy choices. As for the previous aims, these analyses will utilize a linear mixed model with prescription as the between subjects factor and time as the within-subjects factor, as described above.

#### Tertiary (Exploratory) Aim - Maintenance

The exploratory aim has two parts. Part A is to compare how well the healthy behavior changes produced by the different prescriptions maintain throughout four months of follow-up. The planned analyses will use mixed linear modeling with prescription condition as the between subjects factor and time (prescription weeks 1, 2-3, and follow-ups 1 through 8) as the within subjects factor. Part B is to examine whether the processes listed in Aims 2 and 3 (inelasticity, mood, attentional bias and craving for unhealthy eating and activities) mediate the trajectory toward relapse and account for differences between prescriptions in the behavioral decay curves they yield. Analyses for exploratory aim B will use Baron and Kenny's (1986) test of mediation. If the exploratory aim A analyses establish that prescriptions affect the rate at which healthy lifestyle gains decay, then regression analyses will test whether: a) condition affects behavioral and psychological process mediators; b) process mediators affect healthy lifestyle decay curve. If all conditions are met, the test of mediation will be whether behavioral and psychological process mediators fully or partially explain the effect of condition on relapse curves.

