### Analytic Plan

The primary analytic plan is designed to determine which behavioral prescription maximizes attainment of healthy lifestyle behavior change from baseline through prescription phase. The secondary analytic plan is to learn which prescription favorably influences behavioral and psychological processes, i.e., by fostering healthy substitutive or complementary change in lifestyle behaviors, fostering increased elasticity of unhealthy choices and increased inelasticity of healthy choices on the Want Task, and fostering increased self-efficacy, attentional bias, craving, and positive mood in association with healthy choices. The tertiary, exploratory, analytic plan is to examine maintenance of healthy lifestyle change. Distributions of all dependent variables will first be examined to search for outliers and to assess normality, with transformations undertaken as appropriate.

Outcomes will be evaluated within the context of three competing alternative hypotheses. The *familiarity hypothesis *posits that healthy simultaneous change in eating and activity will be maximized by the customary prescription to decrease intake of saturated fat and increase physical activity. The rationale is that this prescription reflects usual dieting and exercise practices, with which most adults have prior experience. The *behavioral economic *(optimal substitution-complementarity) *hypothesis *posits that healthy simultaneous change in eating and activity will be maximized when the prescription is to increase FVs while decreasing recreational screen time. The *low **inhibitory demand hypothesis *posits that healthy simultaneous change in eating and activity will be maximized when the prescription requires no inhibition/suppression of any rewarding eating or activity behaviors. This hypothesis predicts that the prescription to increase FV and PA will most improve healthy lifestyle behaviors because it requires no inhibitory self-control over high-rate, pleasurable eating and activity behaviors.

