### Sample Size and Power

The effect size calculations assume a two-sided alpha set at .05 and were estimated for a power of .85.

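### The causal-steps mediation test sits behind a total-effect gate, which can only lower power to detect mediation; the loss is modest if prescriptions differ clearly in decay and large if they differ little

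*Protocol article*

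**What the plan says.** The section Tertiary (Exploratory) Aim - Maintenance has two parts. Part A compares prescriptions on maintenance with a mixed model. Part B asks whether the process measures "mediate the trajectory toward relapse and account for differences between prescriptions in the behavioral decay curves they yield".

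The method for Part B is fixed by name: "Analyses for exploratory aim B will use Baron and Kenny's (1986) test of mediation". It is conditional on Part A: "If the exploratory aim A analyses establish that prescriptions affect the rate at which healthy lifestyle gains decay, then regression analyses will test whether". Two links are then tested, from prescription to each mediator and from each mediator to decay. Only after that comes the mediation judgement: "If all conditions are met, the test of mediation will be whether behavioral and psychological process mediators fully or partially explain". What is to be explained there is how prescriptions differ in relapse. The section names no estimate of the indirect effect and no interval for it.

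The Analytic Plan states the status of the aim: "The tertiary, exploratory, analytic plan is to examine maintenance of healthy lifestyle change".

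**The concern.** Three significance tests stand in series before mediation is judged: the total effect of condition on decay, condition to mediator (path a), and mediator to decay (path b). Evidence for an indirect effect needs only the last two. The first is an extra hurdle, so it cannot raise power. Under complete mediation the total effect is the product a × b, which is smaller than a whenever b is below 1, so the gate is then often the weakest of the three tests. If two mediators work in opposite directions, or a mediator works against a direct effect, the total can be near zero while the mechanism is real.

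The closing classification adds a second problem. In usual causal-steps practice, full mediation is declared when the direct effect is no longer significant. A small or depleted sample makes that more likely, so weaker data favour the stronger statement.

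At stake is what the trial can say about why gains decay. Part B asks about the relapse trajectory as well as about differences between prescriptions, and the gate serves only the second question.

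**Working it through.** **Inputs from the article.** 200 participants, 50 per arm, contrasts of one condition against the other three, planning effect 0.5, and pilot effects of .66, .63, .21 and .47 (Sample Size and Power, Primary Aim). "The effect size calculations assume a two-sided alpha set at .05" and "were estimated for a power of .85" (Sample Size and Power). Pilot effects of condition on mood, a candidate mediator: .34 and .35 (Sample Size and Power, Secondary Aim). No effect size, power or dropout rate is given for decay or mediation.

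**The plan's own figure.** One arm against three has standard error √(1/50 + 1/150) = 0.163. At 0.5 SD the non-centrality is 0.5/0.163 = 3.06, and power is Φ(3.06 − 1.96) = 0.865 (0.861 by the non-central t). The stated .85 therefore reproduces for one against three. A 50 v 50 comparison would give 0.705.

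**Power of the gate alone.** The article does not say whether Part A must succeed on a 1-df contrast or on the 3-df omnibus test, so both are shown.

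| Total effect on decay | Contrast gate | Omnibus gate |
|---|---|---|
| 0.5 SD | 0.86 | 0.72 |
| 0.3 SD | 0.45 | 0.30 |

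**Gated against ungated detection.** The simulation used 3,000 runs per cell, four arms of 50, unit within-arm SDs, one arm differing from the other three, and all tests at two-sided .05. The gated rule needs total effect, a and b all significant. The ungated rule needs a and b only, and stands in for an interval on the indirect effect. Path sizes are assumptions: a = 0.34, 0.5, 0.8 SD and b = 0.2, 0.3, 0.4, 0.6. Entries are gated power divided by ungated power, as a range over these paths.

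| Total effect on decay | Contrast gate | Omnibus gate |
|---|---|---|
| 0.66 SD | 0.98-1.00 | 0.93-0.99 |
| 0.5 SD | 0.85-0.96 | 0.72-0.90 |
| 0.3 SD | 0.44-0.63 | 0.31-0.49 |
| a × b (complete mediation) | 0.09-0.84 | 0.07-0.69 |
| 0 (opposing direct effect) | about 0.04-0.07 | about 0.04-0.07 |

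The losses are one minus these shares. At 0.5 SD they are 4-15% and 10-28%. At 0.3 SD they are 37-56% and 51-69%, together 37-69%. Under complete mediation the share kept is below one half in 10 of 12 path combinations (contrast) and 11 of 12 (omnibus).

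**One case in full.** With a = 0.5, b = 0.4 and the contrast gate, ungated power is 0.86. Gated power is 0.77 at a total of 0.5 and 0.44 at 0.3 (0.42 in a repeat with 8,000 runs). Under complete mediation, with total 0.5 × 0.4 = 0.2, it is 0.22.

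**With the article's mood effect.** Take a = 0.35, complete mediation and b assumed at 0.3, 0.4 and 0.6. The total is 0.105, 0.14 and 0.21 SD. Gated power is 8%, 10% and 17%; ungated power is 55%, 58% and 58%.

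**With dropout.** At 40 completers per arm (an assumption) and a total of 0.5, the gated rule keeps 0.78-0.93 (contrast) or 0.62-0.85 (omnibus).

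**The full/partial label.** Set the total at 0.5 and the true direct effect at 0.3, so 0.3/0.5 = 60% of the effect is unmediated. Among runs that pass all steps, the direct effect is non-significant in 50% with 50 per arm and 54% with 40 per arm. A repeat with a = 0.5 and b = 0.4 gives those figures when the residual SD of the outcome is 1, and 45% and 51% when its within-arm SD is 1. On either scaling, about half of these mostly unmediated cases would be called full mediation, and the share rises as data are lost.

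**The case against.** A reader might infer that the gate discards most of the power, or that the mechanisms will usually go untested. The article supports neither.

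- Cases with 13-23% gated against 81-91% ungated detection can be built, for example complete mediation with standardised paths (.20, .30), (.26, .26) and (.22, .40). Those products are correlations of .060, .068 and .088. Dividing by the SD of a 50/150 indicator, .433, gives total effects of only 0.14, 0.16 and 0.20 SD, where the total-effect test alone has about 13-24% power. All lie below the smallest pilot effect in the article (.21). At the planning value of 0.5 most of the power is kept. That value was set for change in the primary outcomes, not for decay, so it does not settle the matter either way.
- The Secondary Aim tests condition effects on elasticity, substitution, attentional bias, craving, self-efficacy and mood in their own models, with no decay gate. Only their link to decay is gated.
- Looking for an explanation of differences in decay once a difference is shown is coherent, and that is part of what Part B asks.
- The article prints no rule for telling full from partial mediation, and a fuller document may add an interval. The criticism of the label is therefore conditional on the usual reading.

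These points limit the size and weight of the concern. They do not remove it: the method and the gate are stated choices, the direction of the loss is certain, and the gate does not serve the question about the relapse trajectory.

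**Conclusion.** The concern holds in limited form. Causal steps behind a total-effect gate lower the power to detect mediation of decay. The loss is modest at a total effect of 0.5 SD, substantial at about 0.3 SD or less or under complete mediation with small to moderate paths, and nearly complete when effects offset. Which case applies cannot be read from the article, because it gives no effect size for decay.

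The figures rest on assumed path sizes, a single mediator, decay treated as one continuous outcome, and joint significance of the two paths in place of a bootstrap interval. Severity is minor: the aim is tertiary and exploratory, and no primary or secondary conclusion depends on it.

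**What to change.** For each of the three planned condition contrasts, estimate the indirect effect on decay (product of the two paths) with a percentile bootstrap 95% confidence interval, whatever Part A shows. Report it as exploratory, alongside the total and direct effects. Remove the condition on Part A and drop the full/partial classification.

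This takes about one sentence of analysis wording and uses the same data. The cost is a little more analysis and more exploratory estimates to report, so they should be presented as estimates with intervals and not as confirmed mechanisms.

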#### Primary Aim: Healthy Lifestyle

The outcomes for the primary aim are the z-scores for fruit and vegetables (FV), saturated fat (Fat), physical activity (PA) and sedentary activity (Sed) separately and averaged to form the composite healthy lifestyle score. Using pilot data to compare any one treatment condition to the other three, we found average effect sizes equal to .66, .63, .21 and .47 for change in FV, PA, Sed, and Fat, respectively. Therefore, we anticipate that we will have effect sizes approximately equal to .5 for the three comparisons on each outcome variable. Given an effect size of .5, a total of 200 participants, 50 per group, will yield adequate power for testing the three contrasts.

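### The exploratory mediation analysis ends in a full-or-partial verdict with no margin or interval, so a remaining direct effect of about half the total could often be labelled as none

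*Protocol article*

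**What the plan says.** The protocol article, under Tertiary (Exploratory) Aim - Maintenance, splits the aim in two. Part A compares how well the prescriptions' gains last. Part B asks whether process measures mediate relapse. The method is fixed: "Analyses for exploratory aim B will use Baron and Kenny's (1986) test of mediation".

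It runs behind gates. The first is "If the exploratory aim A analyses establish that prescriptions affect the rate at which healthy lifestyle gains decay". Condition must then affect the mediators, and the mediators must affect the decay curve. If these conditions are met, the closing step is that "the test of mediation will be whether behavioral and psychological process mediators fully or partially explain the effect of condition on relapse curves".

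The section gives no margin, interval or proportion mediated, and it does not state what separates 'fully' from 'partially'. The Analytic Plan sets the standing of the aim: "The tertiary, exploratory, analytic plan is to examine maintenance of healthy lifestyle change". Sample Size and Power gives no figure for this analysis.

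**The concern.** To say that a mediator fully explains a condition effect is to say that the effect left after adjustment for the mediator is zero. In the causal-steps approach that label is conventionally given when the adjusted condition effect is no longer significant. A null hypothesis is then accepted because it was not rejected, with nothing to say how large a remaining effect would contradict the claim.

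This differs from low power to find an indirect effect. Here the earlier steps have all succeeded, and the error is a false statement that nothing else is at work. The trial could report that one measured process accounts for all of the difference between prescriptions in relapse when a substantial part runs outside it.

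**Working it through.** **Inputs from the protocol.** Sample size and effect: "Given an effect size of .5, a total of 200 participants, 50 per group, will yield adequate power for testing the three contrasts". Contrast: "Using pilot data to compare any one treatment condition to the other three", so 50 against 150. Error rates: "The effect size calculations assume a two-sided alpha set at .05 and were estimated for a power of .85".

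**Assumptions of mine.** Total condition effect on the decay measure .5 SD, borrowed from the primary aim ("we anticipate that we will have effect sizes approximately equal to .5 for the three comparisons on each outcome variable"); one mediator with SD 1; within-arm outcome SD 1; condition-to-mediator path *a* from .35 to 1.0 SD; mediator-to-outcome slope *b* set so that *a·b* is the mediated part; complete follow-up.

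**Step 1: reproduce the plan's power.** SE = √(1/50 + 1/150) = .163 SD. Power = Φ(.5/.163 − 1.96) = Φ(1.10) = .865 (.861 with the noncentral t). The stated .85 needs 48 in the single arm, and 50 are planned. The figure reproduces for one against three. A pairwise 50 against 50 comparison gives .705.

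**Step 2: what a direct effect of zero would exclude.** Ignoring the mediator's influence on precision, the 95% half-width is 1.96 × .163 = .32 SD, which is .32/.5 = 64% of the assumed total effect. The mediator changes this by the factor √[(1 − b²)(1 + .1875a²)], where .1875 = .25 × .75. The first term is the variance the mediator removes and the second is its collinearity with condition. With half of the effect mediated (*a·b* = .25):

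| a | b | 95% half-width (SD) |
|---|---|---|
| .35 | .714 | .23 |
| .5 | .5 | .28 |
| .8 | .3125 | .32 |
| 1.0 | .25 | .34 |

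A margin of half the total effect (.25 SD) is out of reach except where the mediator is very strongly tied to the outcome, and then only if the estimate is close to zero.

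**Step 3: chance that the direct effect is non-significant.** Without gates this is 1 − Φ(d/.163 − 1.96), where d is the remaining effect. At d = .25 it is 1 − Φ(−.43) = 67%; at d = .40 it is 1 − Φ(.49) = 31%. It reaches 50% at d = .32 SD, or 64% of the total.

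With gates, I simulated trials (10,000 per setting) and kept those in which the total effect, path *a* and path *b* were all significant at two-sided .05. The ranges run over *a* = .35 to 1.0.

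| Share of effect unmediated | No gates, 50 v 150 | Gates passed, 50 v 150 | Gates passed, 50 v 50 |
|---|---|---|---|
| 80% | 31% | 23-49% | 39-73% |
| 75% | 37% | 28-51% | 41-73% |
| 60% | 55% | 38-60% | 53-75% |
| 50% | 67% | 41-67% | 58-80% |

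Fixing the slope at .3-.5 instead (50 v 150) gives about 56-63% with half unmediated and 29-34% with 70% unmediated.

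**Step 4: counting all trials, not only those past the gates.** With half mediated and slope .4, reducing N from 200 to 80 raises the conditional rate from 59% to 71%. The gates fail more often, however, and the overall rate of a false 'full' label falls from about 50% to about 27%.

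**Step 5: a mediator with pilot data.** The Secondary Aim power section gives mood effects of .34 and .35. With *a* = .35 and slopes .3-.5, mood carries .105/.5 = 21% to .175/.5 = 35% of the effect. About half of the trials pass all gates, and a false 'full' label arises in about 12-19% of all trials.

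**The case against.** The strongest objection is that the criticised rule is not in the text. The section never says that 'fully' means a non-significant direct effect, and its wording does not forbid reporting the estimate with an interval. This stands as a limit: the criterion is inferred from the named method. It does not remove the point, because the protocol itself fixes both the method and the two-way verdict.

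A related objection is that margins and bootstrap intervals belong in an analysis plan that is not shown. Their absence alone would indeed be no finding. What is questioned is the stated conclusion.

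The inputs are also borrowed. The .5 SD refers to the primary aim, and Part A uses a four-level condition factor, not one against three. The percentages are therefore illustrative. A smaller total effect would generally raise them, as would pairwise comparisons.

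Three stronger readings are tempting and not supported:
- A reader might infer that a large remaining effect will usually be reported as none. At 75-80% unmediated on the one-against-three contrast, this happens in roughly a quarter to a half of the trials that pass the gates.
- A reader might infer that poorer data make the stronger claim more likely. That holds only among trials past the gates; the overall rate falls (Step 4).
- A reader might take mood as the natural example of a mediator carrying half of the effect. The pilot figures of .34 and .35 do not fit that with slopes of .3-.5 (Step 5).

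**Conclusion.** The point holds as a minor one. The plan offers complete mediation as a conclusion without any bound on what remains, and at 200 participants the data could seldom support it. Under the assumed .5 SD total effect and 50 against 150, trials that pass the earlier steps would be labelled 'full' in roughly 40-67% of cases with half of the effect unmediated, and in roughly 25-50% with 70-80% unmediated. This rests on the conventional reading of the causal-steps test, the borrowed effect size, the assumed paths and complete follow-up. The aim is tertiary and exploratory, and no primary conclusion depends on it.

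**What to change.** Remove the full-or-partial decision from Part B. Report the indirect effect and the remaining direct effect, each with a 95% confidence interval (for example, bootstrap). State that complete mediation will not be claimed unless the interval for the direct effect lies within a margin set in advance, such as a stated fraction of the total effect.

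The cost is one or two sentences, with no new data or participants. The downside is small: with 200 participants a claim of complete mediation will rarely be possible.

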### Sample Size and Power

The effect size calculations assume a two-sided alpha set at .05 and were estimated for a power of .85.

#### Primary Aim: Healthy Lifestyle

The outcomes for the primary aim are the z-scores for fruit and vegetables (FV), saturated fat (Fat), physical activity (PA) and sedentary activity (Sed) separately and averaged to form the composite healthy lifestyle score. Using pilot data to compare any one treatment condition to the other three, we found average effect sizes equal to .66, .63, .21 and .47 for change in FV, PA, Sed, and Fat, respectively. Therefore, we anticipate that we will have effect sizes approximately equal to .5 for the three comparisons on each outcome variable. Given an effect size of .5, a total of 200 participants, 50 per group, will yield adequate power for testing the three contrasts.

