#### Primary Aim - Healthy Lifestyle

The first aim is to test our three alternative hypotheses about the optimum way to advise people to make two healthy behavior changes simultaneously, one in eating and one in activity. For this, we will use a linear mixed model (LMM) for longitudinal data [43] treating the composite health lifestyle z-score as the dependent variable, and including prescription condition as a between subjects factor and time as a within-subjects factor. The hypotheses predict a condition × time interaction, indicating that some conditions are more effective than others at bringing about healthy behavior change. If the overall omnibus F test of the condition × time interaction is significant, three planned comparisons will be performed to test the three competing hypotheses following procedures recommended by Rosenthal, Roscoe, and Rubin (2000) [44]. These comparisons will contrast the groups based on change over time for the composite healthy lifestyle z-score. Additionally, if the condition × time interaction is significant for the composite z-score, we will follow-up the overall test with separate tests of the interaction effect on each health behavior.

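### The planning effect of about .5 is extended to every outcome, but the plan's own pilot average for sedentary time is .21, where a one-versus-three contrast has about 25% power

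*Protocol article*

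**What the plan says.** Under Sample Size and Power, the protocol article sets the general terms: "The effect size calculations assume a two-sided alpha set at .05 and were estimated for a power of .85". The subsection Primary Aim: Healthy Lifestyle then names five outcomes for the primary aim: the z-scores of the four behaviours taken separately, and their average, the composite.

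The basis is a pilot. "Using pilot data to compare any one treatment condition to the other three", the authors report, "we found average effect sizes equal to .66, .63, .21 and .47 for change in FV, PA, Sed, and Fat, respectively". From this they conclude that "we anticipate that we will have effect sizes approximately equal to .5 for the three comparisons on each outcome variable", and they close with "Given an effect size of .5, a total of 200 participants, 50 per group, will yield adequate power for testing the three contrasts".

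Elsewhere the article makes the composite the primary outcome (abstract, Methods/Design; Healthy Lifestyle Change). The Analytic Plan, under Primary Aim - Healthy Lifestyle, tests the condition by time interaction on the composite and, if it is significant, runs the three planned comparisons on the composite. Under the same condition it adds "separate tests of the interaction effect on each health behavior".

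**The concern.** The text presents .5 as following from the four pilot values. Their mean is .4925, so the figure is reasonable as an average. The sentence, however, assigns it to every outcome, and for sedentary time the only evidence offered is .21, less than half of .5. No reason is given for expecting a larger effect there.

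This matters because the behaviours are to be tested one by one if the composite interaction is significant, and sedentary time is a prescribed target in two of the four conditions (Study Design). A reader who relies on the sample-size section would believe that each behaviour has adequate power. That reader could take a non-significant sedentary result as evidence that sedentary time did not differ between conditions, although the contrast had little chance of detecting an effect of the size seen in the pilot.

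**Working it through.** **Inputs** (all from Sample Size and Power): two-sided alpha .05; target power .85; 50 per group, 200 in total; contrasts of one condition against the other three, so 50 vs 150; planning effect .5; pilot effects FV .66, PA .63, Sed .21, Fat .47. Effects are standardised (SD = 1). The article states no dropout allowance and none is applied.

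**Formula.** Standard error of the contrast in SD units: √(1/50 + 1/150) = .1633. Power ≈ Φ(d/.1633 − 1.960). The noncentral t with 198 degrees of freedom serves as a check.

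**Reproducing the plan's figure.** At d = .5: .5/.1633 = 3.062, and Φ(3.062 − 1.960) = .865 (noncentral t .862). The number needed for .85 is (4/3) × ((1.960 + 1.036)/.5)², which rounds up to 48 per group against the 50 planned. The plan's own claim is therefore recovered.

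**Where .5 comes from.** (.66 + .63 + .21 + .47)/4 = 1.97/4 = .4925. The article does not state this step; the match is inferred.

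**Same method at each pilot value.**

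| Behaviour | Pilot d | d/.1633 | Power (normal) | Power (noncentral t) |
|---|---|---|---|---|
| FV | .66 | 4.042 | .981 | .980 |
| PA | .63 | 3.858 | .971 | .970 |
| Fat | .47 | 2.878 | .821 | .817 |
| Sed | .21 | 1.286 | .250 | .249 |

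**What 50 vs 150 can detect.** The smallest effect with power .85 is (1.960 + 1.036) × .1633 = .489. For Sed at .21, power .85 would need (4/3) × (2.996/.21)², or 272 per group (1,088 in total).

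**Does another comparison rescue Sed?**
- 50 vs 50 at .21: .18.
- 100 vs 100 at .21: .32.
- One-sided .05, 50 vs 150: .36.
- Alpha .05/3, 50 vs 150: .13.
- Assume that the two Sed-targeting conditions share an effect e and the other two have none. Each one-versus-three difference is then 2e/3 in size, so .21 implies e = .315. At 100 vs 100 this gives .315 × √50 = 2.227, and Φ(2.227 − 1.960) = about .60.

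None reaches .85.

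**The composite.** Assume that the four pilot effects apply to the same contrast, in the same direction and on a common SD scale, with equal correlation ρ between behaviours. The composite effect is then .4925/√((1 + 3ρ)/4). At ρ = 1 it is .4925 (power .85), at ρ = .5 it is .62 (power .97), and it is larger at lower ρ. The article does not give ρ.

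**The case against.** The strongest reply is that the trial is sized on its primary outcome, and that this sizing is sound. The composite carries the hypothesis tests, N = 200 reproduces at d = .5, and the power statement is explicitly conditional on .5. No power for sedentary time is printed. All of this stands. A reader might infer that the trial is too small or that the primary analysis lacks power, and the documents do not support that. The reply does not rescue the sentence at issue, which lists the behaviours separately and extends .5 to each.

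Second, the behaviour tests are follow-ups to a significant composite interaction, and each is itself a four-condition interaction test. So .25 is the power of a one-versus-three contrast, the kind that the power section describes, and not of the follow-up test itself. This is correct and limits how the number may be used. Gating decides whether the test is run; it does not enlarge the sedentary effect.

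Third, .21 is an average over one-versus-three comparisons, the pilot's size is not given, and the value for any single contrast is unknown. The .25 therefore cannot be attached to the increase-FV, decrease-Sed condition or to the behavioral economic hypothesis in particular. Under the assumed .315 above, power is about .60, which is much better but still short of .85.

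Fourth, a reader might infer that a null sedentary result would be taken as absence of substitution. The article does not say so. Substitution has its own analysis (Secondary Aim, Analytic Plan) and its own power statement, with an effect size of 1.46 (Secondary Aim, Sample Size and Power).

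Finally, .47 for Fat, with power of about .82, is consistent with an effect of approximately .5 and should not be counted as a failure.

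**Conclusion.** The point holds in a limited form. The claim of an effect of about .5 on every outcome is contradicted by the pilot figure in the same paragraph for one of the four behaviours. By the method that reproduces the plan's own power, the one-versus-three contrast on sedentary time has power of about .25 at the average pilot effect. FV (.98) and PA (.97) are well covered, and Fat (.82) is close to target.

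The result assumes full retention, two-sided .05 without adjustment for three contrasts, and the pilot averages taken at face value. An assumed loss of 10% or 20% would lower the Sed figure to about .23 or .21. The conclusion does not depend on the choice of comparison, because every variant tried leaves Sed well below .85. It does not extend to the sample size at d = .5 or to the composite.

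**What to change.** In Sample Size and Power, Primary Aim: Healthy Lifestyle:

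1. Keep .5 (pilot mean .4925) as the planning effect for the composite contrasts only, and delete the last four words of the sentence that extends it to all outcomes.
2. Report the one-versus-three power for each behaviour at its pilot value: about .98 for FV, .97 for PA, .82 for Fat and .25 for Sed.
3. State that the gated Sed follow-up has low power at the average pilot effect (about .25 for a one-versus-three contrast), and that the smallest effect detectable with power .85 is about .49.

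In the Analytic Plan, Primary Aim - Healthy Lifestyle, keep the planned follow-up test. Add that a non-significant Sed result will be presented with its estimate and confidence interval, and will not be read as evidence of no change.

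The cost is a few sentences. Sample size, design and primary analysis are unchanged. The downside is that the power stated for one of the four behaviours becomes much less favourable than the present text implies.
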